# Brushing RemInder 4 Good oral HealTh (BRIGHT) trial: does an SMS behaviour change programme with a classroom-based session improve the oral health of young people living in deprived areas? A study protocol of a randomised controlled trial

**DOI:** 10.1186/s13063-019-3538-6

**Published:** 2019-07-23

**Keywords:** Dental caries, Caries prevention, Prevention, Behaviour change, Randomised controlled trial, Child dental health, mHealth, Short messaging service

## Abstract

**Background:**

Almost one-half of 12–15 year olds living in deprived areas of the UK have dental caries (tooth decay) with few oral health promotion programmes aimed at children of this age. Mobile phone-based interventions such as short messaging service (SMS) interventions have been found effective at changing certain behaviours and improving health outcomes. This protocol describes the BRIGHT Trial, investigating the clinical and cost-effectiveness of a behaviour change intervention—classroom-based session (CBS) embedded in the curriculum and a series of SMS delivered to participants twice daily to remind them to brush their teeth, compared to usual curriculum and no SMS—to reduce the prevalence of dental caries in young people from deprived areas.

**Objectives:**

To investigate the clinical and cost-effectiveness of a complex intervention to improve the oral health of young people living in deprived areas.

**Methods/design:**

This is a school-based, assessor-blinded, two-arm cluster-randomised controlled trial with an internal pilot trial. Overall, the trial will involve approximately 5040 11–13 year olds in 42 schools with a 3-year follow-up. The trial will take place in secondary schools in England, Scotland and Wales. The primary outcome is the presence of carious lesions in permanent teeth at 3 years. Secondary outcomes are: number of carious teeth, frequency of twice-daily toothbrushing, plaque levels, gingivitis, child health-related quality of life and oral health-related quality of life. A cost-utility analysis will be conducted.

**Discussion:**

The findings of the trial have implications for embedding oral health interventions into school curricula guidance produced by national bodies, including departments for education and dental public health and guideline-development organisations.

**Trial registration:**

ISRCTN registry, ISRCTN12139369. Registered on 10 May 2017.

**Electronic supplementary material:**

The online version of this article (10.1186/s13063-019-3538-6) contains supplementary material, which is available to authorized users.

## Background

Untreated dental caries (tooth decay) is the most prevalent condition worldwide, affecting 2.4 billion people [1]. The consequences for children include pain [2], loss of sleep, problems with eating and speaking and time off school [3–5]. Dental caries has a significant impact on young people’s daily lives with around 50% of 12–15 year olds reporting toothache and around one-quarter of 12–15 year olds reporting difficulty eating [4]. Dental caries can also affect the general health and quality of life of children, interfering with nutrition, school attendance and school performance [6–8]. A recent systematic review found children with one or more decayed teeth had a higher probability of poor school performance and poor school attendance than children free of obvious caries [8].

Dental caries affects an average of one in three 12 year olds in the UK and although it affects all parts of society, it shows a positive, linear association with deprivation [9–11]. In 2013 in England, 32% of 12 year olds experienced dental caries and required treatment, ranging from 46% of those eligible for free school meals (FSM) to 30% of those ineligible. For 15 year olds 44% required treatment, 59% of those eligible for FSM and 43% of those ineligible [4]. Treating oral diseases is expensive, costing NHS England £3.4 billion annually. Children’s tooth extractions alone, carried out under general anaesthesia, and as a result of dental caries, costs an estimated £36 million annually in England [12].

The use of fluoridated toothpaste is considered to have been largely responsible for the dramatic reduction in the levels of dental caries from a mean of 8.4 decayed, missing and filled teeth (DMFT) in 1973 [13] to 1.4 in 2013 [4]. Brushing with fluoridated toothpaste is one of the most highly effective preventive measures [14, 15]. Observational studies have shown current levels of efficacy, frequency and duration of toothbrushing to be inadequate [16–18], increasing the risk of dental caries [9].

Mobile health (mHealth) describes multimedia technologies that interface with healthcare delivery and are supported by mobile devices, almost exclusively mobile phones [19]. In 2017, 86% of 12–15 year olds in the UK owned a mobile phone [20], providing the potential to deliver large-scale health behaviour change interventions. While young people of lower socio-economic status are subject to inequality in access and use of health services, research suggests they have equivalent mobile phone access to their more affluent peers [21]. Short messaging service (SMS) are short text messages sent from computers, phones or other mobile devices usually to phones and are the most widely studied mHealth interventions [19, 22].

A recent systematic review of preventive health behaviour change SMS interventions found a small but statistically significant weighted mean effect size for the impact of SMS on preventive health behaviour change (d = 0.24) with positive effect of SMS interventions in 11 of the 35 included studies, with a further 13 studies having mixed effects [23]. The key features of SMS interventions include duration, tailoring, targeting of the content and how SMS are used along with other activities [23]. The duration of interventions typically ranged from 1 to 66 weeks with a median duration of 12 weeks. There was some suggestion that interventions lasting 6–12 months were associated with greater effects than shorter interventions. The frequency of messages varied from five times per day to once a month depending on the expected frequency of the targeted behaviour [23]. The limitations of existing studies included a lack of a specified theoretical framework, insufficient power to detect change, only short-term follow-up after the end of the intervention, low retention rates and failure to blind assessors [23–25]. It was recommended that future studies ensured the intervention, including the SMS, was developed rigorously, the SMS were written to be appropriate for the target population and the SMS were tailored to individuals according to their age and gender and used the participant’s name.

Although the mobile phone has been investigated as a vehicle for health behaviour change using SMS interventions, there is a paucity of research with adolescents and involving oral health behaviour change [26]. One recent study, of unemployed young people aged 18–24 years in New Zealand, investigated the Keep on Brushing (KOB) programme of weekly SMS and free toothbrushes/toothpaste, seeking to boost motivation [27, 28]. The KOB intervention was underpinned by the Health Belief Model [29]. This study was conducted in a branch of the New Zealand Government’s employment and beneficiary services and 171 participants were recruited and completed a baseline survey and then received a series of motivational SMS over 10 weeks. Self-reported toothbrushing frequency was the primary outcome measure. Other socio-demographic data (age, gender, ethnicity, employment status) and method-specific (level of attrition, distribution of successful text messages deliveries, active withdrawal) variables were also collected. Self-reported toothbrushing of twice or more per day increased from 51% at baseline to 70% at week 3, 74% at week 6, and 73% at week 9. No important differences were noted between ages, gender or ethnic groups, although attrition was relatively high with only 26% participating by week 9. The authors concluded that motivational SMS improved the self-reported oral health of this hard-to-reach group and suggested a randomised controlled trial including a longer intervention with tailoring of the messages was needed.

The aim of this study is to establish the clinical and cost-effectiveness of a SMS behaviour change programme to improve the oral health of young people living in deprived areas.

The main trial will:investigate the effect of the intervention on caries prevalenceinvestigate the effect of the intervention on twice-daily tooth brushing, oral health-related quality of life and oral health behavioursinvestigate the cost-effectiveness of the interventionexplore implementation, mechanisms of impact and context through a process evaluation

## Methods/design

### Study design

The BRIGHT trial is a multi-centre, school-based, assessor-blinded, two-arm cluster-randomised controlled trial (RCT).

The population being investigated are pupils in schools with above average percentage of pupils eligible for free school meals (FSM). The BRIGHT intervention is based on the New Zealand KOB study intervention. It is a multi-component, complex intervention with two parts: 1) a short classroom-based session (CBS) embedded in the curriculum; and 2) a series of follow-up twice-daily SMS. Pupils in the control group will continue to receive routine education and no text messaging, and the primary outcome is the presence of caries.

### Procedure

#### Study setting

The trial aims to recruit 5040 young people, aged 11–13 years (year 7 and year 8 in England/Wales; S1 and S2 in Scotland) from 42 schools across Scotland, England and Wales with above the national average percentage of pupils eligible for FSM. These year groups have been chosen purposefully to minimise disruption to English and Welsh GCSE and Scottish Qualifications Authority National 5 exam years, and also to confine 3-year follow-up to within the school setting to avoid the need to follow participants to further education settings.

#### School eligibility (inclusion/exclusion criteria)

To be eligible for participation, schools must:be located in Scotland, England (South Yorkshire and West Yorkshire), or South Walesbe state fundedhave pupils aged 11–16 years oldhave at least 60 pupils per year grouphave above the national average percentage (for each devolved nation) of pupils eligible for FSM

Schools will be ineligible for inclusion if they are:in Special Measures where the school is judged by the Office for Standards in Education, Children’s Services and Skills to be failing, or likely to fail, to provide an acceptable standard of educationdue to close

Eligible schools will be identified based on data from the Department for Education’s register of educational establishments in England and Wales and Education Scotland. Schools will be approached by local research teams and invited to take part.

#### Participants

Participants are young people aged 11–13 years old at baseline and attending schools with above the national average percentage of pupils eligible for FSM.

#### Young person (participant) eligibility (inclusion/exclusion criteria)

Young people will be eligible for inclusion if they are:a pupil at a participating school, andaged 11–12 years (in year 7 in England/Wales or S1 in Scotland) or 12–13 years (in year 8 in England/Wales or S2 in Scotland)

Young people will be ineligible for inclusion if:they have no functioning mobile telephone of their own, ortheir parent/carer does not want them to be part of the trial and they opt out

#### Young person (participant) recruitment

Recruitment strategies have been based on consultation with young people through a youth organisation particularly concerned with hard-to-reach young people (Children and Young People’s Empowerment Project (Chilypep)), teachers and head teachers, a school welfare officer and school nurse and from learning during the internal pilot trial. A young person forum has contributed to the design of the trial and successfully ran throughout the internal pilot trial. This forum will continue to advise on participant recruitment and the best ways of optimising continued engagement with hard-to-reach pupils during the trial.

#### Consent procedure

Parents/carers will have the opportunity to state that they do not want their child to participate (opt out), by completing and returning an opt-out form to their child’s school. Eligible young people whose parents/carers have not opted them out of the research will then be invited to take part in the trial. The young people who agree will be asked to sign a consent form by members of the local research team or teachers.

All young people who complete the baseline questionnaire and dental assessment will be given a £10 voucher to thank them for their time; all young people who complete the follow-up questionnaire and dental assessment will be given a £5 voucher as a thank you.

#### Study procedure

##### Randomisation

Allocation will take place within schools by randomising schools 1:1 to one of two regimes:11–12-year-old pupils (year 7 in England and Wales/S1 in Scotland) to receive the intervention and 12–13-year-old pupils (year 8 in England and Wales/S2 in Scotland) to act as the control group, or12–13-year-old pupils (year 8 in England and Wales/S2 in Scotland) to receive the intervention and 11–12-year-old pupils (year 7 in England and Wales/S1 in Scotland) to act as the control group

An allocation sequence, stratified by school using blocks of size two [30], will be generated by an independent statistician. This sequence will be retained by the statistician and will not be accessible to other members of the trial research team. Once a school is ready to be randomised, following collection of their baseline data, the year groups within that school will be randomised by assigning their year 7 and year 8 cohorts (in that order) to the next block in the allocation schedule. The research team and schools will then be informed of which year group has been allocated to receive the BRIGHT intervention and which has been assigned to the control arm. Since the statistician performing the allocation and the teams recruiting the schools are completely separate, and the allocation schedule cannot be known to anyone but the statistician in advance of randomisation, allocation concealment is assured.

##### Blinding

Given the nature of the intervention, it will not be possible to blind schools or participants (pupils) to their group allocation; however, clinical examinations will be performed by a trained and calibrated dentist blind to the allocation of the pupils, as far as possible. It is possible that pupils may unblind the assessors but they will be encouraged not to discuss the intervention with the dental team to minimise this risk. We shall ask the dental teams to record whether they became unblinded to the pupil’s allocation.

### Intervention and comparison (control)

The aim of the intervention is to increase toothbrushing frequency with a fluoride toothpaste and thereby reduce the likelihood of the development of dental caries. The intervention consists of two components: (1) a CBS delivered by teachers in the schools’ curricula followed by (2) a series of twice-daily SMS to mobile phones. The intervention meets the Medical Research Council definition of a complex intervention in terms of the interactions between components and the difficulty of behaviours required by those receiving the intervention [31]. The control group will not receive the CBS or SMS messages. The KOB intervention has been refined to be more acceptable to young people and informed by recent behaviour change theory [32].

#### CBS

Teachers will deliver the single CBS (50 min in duration) in the school environment to participants in the intervention arm. The schools will receive a teacher’s guide that will outline the learning intentions and success criteria for the lesson, in addition to the appropriate teaching resources in order to deliver the lesson. The lesson has been quality assured in England, Scotland and Wales. The number of schools that report delivering the CBS will be reported.

#### SMS

The schedule of SMS was developed using young people’s own words and will reinforce the messages from the CBS. SMS will be provided via mobile phones twice daily according to the recommended frequency of toothbrushing with a fluoride toothpaste. Participants will be reminded to inform the study team of any changes to their mobile phone number. When participants wish to stop receiving text messages, they can text STOP for free at any time. Messages will also be re-started on request. The number of SMS messages received by the pupils will be summarised descriptively.

### Outcome measures

#### Primary outcome

The primary outcome for this trial is the presence of at least one treated or untreated carious lesion in any permanent tooth measured at the young person-level using the permanent tooth index 'DMFT' (Decayed, Missing and Filled Teeth) where decay is measured as carious lesions extending into dentine - International Caries Detection and Assessment System (ICDAS) levels 4-6 [33], at three years follow-up. The outcome will be measured cross-sectionally at 3 years, and is regardless of the presence or absence of caries in the teeth at baseline.

#### Secondary outcomes

Caries (D_4–6_ MFT) at 2 years: the presence of at least one treated or untreated carious lesion into dentine in permanent teeth (ICDAS levels 4–6) at 2 years follow-up.Caries (D_1–6_ MFT) at 2 and 3 years: the presence of at least one carious lesion in permanent teeth (ICDAS levels 1–6) at 2 and 3 years follow-up.Number of carious teeth at 2 and 3 years: The number of permanent teeth with any treated or untreated carious lesions (ICDAS 1-6, and caries into dentine 4-6) at 2 and 3 years.Twice-daily toothbrushing: self-reported toothbrushing frequency using validated questions from the national Child Dental Health surveys at baseline, 6 months and 1, 2 and 3 years. To validate the self-reported measure, two proxy clinical objective indicators will be collected: (i) clinically assessed plaque levels using Turesky’s modification of the Quigley Hein Plaque Index [34, 35]; and (ii) clinically assessed gingivitis using gingival bleeding (modification of the Gingival Index of Löe) [36] and mean number of bleeding gingival sites per child. The clinical measures will be carried out at baseline and at the end of years 2 and 3.

#### Other outcomes

Health related quality of life (HRQoL) will be assessed using the Child Health Utility 9D (CHU9D) [37]. This will be measured at baseline and at years 1, 2 and 3.Child oral HRQoL will be assessed using the CARIES-QC. This will be measured at baseline and at years 1, 2 and 3.

Oral health behaviours will be assessed based on self-reported data from young people using questions from the national Child Dental Health Survey [4, 38] on diet, use of dental services and other forms of fluoride use, which will allow assessment of confounding. This will be measured at baseline, 6 months and at years 1, 2 and 3.

For cost-effectiveness, health service resource use will be assessed for the health economic analysis based on data reported by parents via a questionnaire. This will be measured at baseline and at years 1, 2 and 3. Resource use may also be estimated from routine data sources.

Impact on school attendance will be measured by asking schools to provide the attendance record of all participating young people at baseline and at 1, 2 and 3 years.

The impact of the intervention on young people from deprived areas specifically will be assessed. Young people’s eligibility for FSM will be collected from their school and Income Deprivation Affecting Children Index (IDACI) scores will be calculated where possible from participant’s home postcodes.

A mixed method process evaluation will also be conducted to explore implementation, mechanisms of impact and context of the complex intervention [39].

Figure 1 describes the schedule of recruitment, assessments and intervention delivery.

**Fig. 1 Fig1:**
[figure not shown]
Schedule of enrolment, interventions and assessments

#### Data collection

Data collection will be carried out in the secondary schools under standard dental epidemiological conditions and with questionnaires completed by young people in school time and by parents at home.

The University of Dundee and York Trials Unit (YTU) at University of York will act as the data controllers for this study. All information collected during the course of the trial will be kept strictly confidential. YTU and the regional sites will comply with all aspects of the General Data Protection Regulation 2016 applicable in the UK from May 2018. Personal data will be processed under Article 6 (1) (e) (*Processing necessary for the performance of a task carried out in the public interest*) and Special Category data under Article 9 (2) (j) (*Processing necessary for ... scientific ... research purposes)* of the General Data Protection Regulation 2016. Data sharing agreements will be put in place with participating schools.

A unique trial identification number (trial ID) will be generated for each participant, details of which will be entered into the trial management system. All data, from baseline through to final follow-up, will be collected on paper using case report forms (CRFs) and identified solely by the trial ID; they will be scanned at YTU using Teleform data capture software into a bespoke data management system. Both the trial management system and the data management systems are held on secure University of York servers with access limited to specified members of YTU staff. The paper consent forms and paper CRFs will be held separately and securely in a controlled access area in locked cabinets.

A young person’s mobile phone number, along with their nickname (to which text messages will be addressed) and text message time preference, will be uploaded by YTU directly to the Health Informatics Centre (HIC), University of Dundee. No other details will be uploaded. HIC Services operates a secure Safe Haven environment with strong data governance for the provisioning of data.

##### Sample size

The estimated proportion of UK 12 year olds with caries is 32%, with estimates of 46% for those eligible for FSM and 30% for those not eligible for FSM [4, 40]. Based on a systematic review of interventions for caries prevention to increase the frequency of toothbrushing [41], an absolute reduction in the proportion of young people with caries of 8% might be expected with this intervention. An individually randomised trial powered at 90% (5% two-sided α) to detect a reduction in the proportion of young people with caries from 32% to 24% would require a sample size of 1320. Since this is a cluster trial, this figure needs to be inflated to account for the correlation of the outcomes within schools, as measured by the intraclass correlation coefficient (ICC). Few estimates of a school-level ICC are available for dental data. In a previous study evaluating a behaviour change programme for preventing dental caries in primary schools, an ICC of 0.01 was used, which was estimated using their own unpublished data [42]; a more conservative ICC of 0.02 has been chosen for this trial.

Additionally, since randomisation is taking place at the level of the year group, and not at the school-level, there is the potential for some contamination (e.g. pupils in the year group assigned to the control arm receiving information about the intervention from pupils in the other participating year group assigned to receive the intervention). There is an argument to therefore increase the sample size further to account for some level of contamination, which has the potential to dilute the treatment effect. We have assumed only partial contamination effects (i.e. those contaminated gain half the treatment benefits as it is unlikely that any pupil in the control group would receive all the intervention) for 27% of the control group pupils (based on findings from the internal pilot phase of the trial). In total, 40 schools are required assuming within-school (year group level randomisation), an average of 60 pupils per year group, an ICC of 0.02, and 20% pupil-level attrition at follow-up. This would give us 90% power (5% two-sided α) to detect an 8% absolute reduction, from 32% to 24%, in the proportion of pupils with caries. An attrition rate of 20% was estimated as the pupils will continue to be at school for the duration of the trial so it will be possible to reach and engage with them through the school and in an environment they recognise as educational and supporting their interests. Overall, 42 schools will be recruited to allow for the potential that a small number of schools may withdraw.

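### The 90% power claim rests on 32% v 24%, an age-12 caries prevalence; the outcome is a cumulative index read at about 14 to 16, where 24% would lie below the expected starting level

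*Protocol article*

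**What the plan says.** The Sample size section opens with "The estimated proportion of UK 12 year olds with caries is 32%, with estimates of 46% for those eligible for FSM". It then takes an absolute reduction of 8 points from a systematic review. For individual randomisation at 90% power and two-sided 5%, it says this "would require a sample size of 1320". After allowing for clustering, contamination and attrition it arrives at 40 schools (42 to be recruited) and claims 90% power "to detect an 8% absolute reduction, from 32% to 24%, in the proportion of pupils with caries".

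Pupils are 11 to 13 at baseline (Participants). The Primary outcome section defines the outcome as at least one treated or untreated lesion into dentine (ICDAS 4 to 6) in a permanent tooth at three years, and adds that this "is regardless of the presence or absence of caries in the teeth at baseline".

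The Background gives the prevalence near the endpoint age: "For 15 year olds 44% required treatment, 59% of those eligible for FSM and 43% of those ineligible". The Abstract says: "Almost one-half of 12–15 year olds living in deprived areas of the UK have dental caries". The Sample size section uses neither figure. School eligibility requires an above-average percentage of pupils eligible for free school meals (FSM).

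**The concern.** The control rate belongs to the start of follow-up, but the outcome is measured at the end. A pupil with a dentine lesion at entry remains a case at three years, because a filled or extracted tooth still counts. Prevalence in a followed group can therefore only stay level or rise, barring examiner error or selective loss. If about 32% are cases at entry, or more given how schools are chosen, the intervention arm cannot stand at 24% three years later.

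The power statement fixes how the result will be read. A null finding would be set against 90% power for 32% v 24%, a pair of rates that cannot arise. The pair also looks like a one-quarter relative reduction (8/32). In fact the intervention can act only on lesions that arise after entry, so the same 8 points is a much larger share of what is preventable.

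**Working it through.** **Inputs from the article.** Two-sided 5%, power 90%; 60 pupils per year group, one year group per arm in each school; ICC 0.02; attrition 20%, leaving 48; 27% of controls gain half the benefit. Age 12: 32% overall, 46% FSM-eligible, 30% not. Age 15: 44%, 59%, 43%.

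**1. The plan's own figures.**
- Per arm: n = [1.96√(2p̄(1−p̄)) + 1.2816√(p₁(1−p₁) + p₂(1−p₂))]² / (p₁−p₂)². For 32% v 24% this is 659.9, so 660 per arm and 1320 in total, as stated.
- Contamination: the control rate becomes 0.32 − 0.27 × 0.5 × 0.08 = 0.3092. Against 0.24 this needs 873 per arm.
- Design effect: 1 + 59 × 0.02 = 2.18. Schools: 873 × 2.18 / 0.8 / 60 = 39.65, so 40, as stated. Power at 40 schools is 90.3%.

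The arithmetic is right. The question is the choice of rates.

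**2. Can 24% occur?** The overall age-12 figure implies an FSM share f with 30 + 16f = 32, so f = 12.5%. Schools above the average share should start at or above 32%. For illustration only, a share of 25% (my assumption) gives 30 + 0.25 × 16 = 34% at age 12 and 43 + 0.25 × 16 = 47% at age 15. The target of 24% is at least 8 points under the expected starting level.

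**3. Same 8 points at the age-15 rate, unadjusted.** Individually randomised, 44% v 36% needs 786 per arm (1572). With contamination the control rate is 0.44 − 0.135 × 0.08 = 0.4292, and 1047 per arm are needed. Effective n per arm is schools × 48 / design effect. I show the plan's design effect (2.18) and the one for the 48 pupils left after attrition (1 + 47 × 0.02 = 1.94).

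| Design effect | Schools for 90% | Power, 40 schools | Power, 42 schools |
|---|---|---|---|
| 2.18 | 47.6 (48) | 84.5% | 86.2% |
| 1.94 | 42.3 (43) | 88.3% | 89.8% |

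At the FSM-eligible rate (59% v 51%), power at 40 schools is 83.1% or 87.2%.

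**4. Share of new cases.** Taking the difference between age groups as new caries: 44 − 32 = 12 points overall, and 13 points within each FSM group (59 − 46; 43 − 30). Eight points is 8/12 = 67%, or 8/13 = 62%, of new cases.

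**5. Allowing for baseline caries.** The Data analysis section adjusts the primary model for baseline caries. Pupils who are cases at entry stay cases and carry almost no information on treatment, so I approximate the model by the caries-free pupils.
- Per year group: 48 × 0.68 = 32.6; design effect 1 + 31.64 × 0.02 = 1.633; effective n per arm 800 at 40 schools and 840 at 42.
- Three-year risk in controls: 12/68 = 17.6%. With 8 points prevented: 4/68 = 5.9%. Contaminated control: 17.6 − 0.135 × 11.8 = 16.1%. Power exceeds 99.9% at 40 schools.
- Difference detectable with 90% power, before contamination: about 4.4 points at 40 schools and 4.3 at 42. The latter is 4.3/12, about 36% of new cases. With the FSM-eligible or non-eligible rates instead, it is 4.2 or 4.5 points at 42 schools.

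**The case against.** The effect taken from the literature is an absolute 8 points, and such a difference is possible at a higher level. This stands. A reader might infer that the trial cannot show an 8-point effect at all, but the document supports that only for the 32% v 24% pair.

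The loss of power is small, and the planned analysis may remove it. This also stands. Unadjusted, the shortfall from 90% at 42 schools is between nearly nothing and 4 points. Once baseline caries is allowed for, power for 8 points is very high, and the detectable absolute difference is smaller than 8. A reader might infer that the trial is underpowered for its own target; the figures do not show that.

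A reader might go further and apply the implied 25% relative reduction to new caries alone. That gives 44% v 41%, with power at 40 schools of about 20% unadjusted and 57% among caries-free pupils. The protocol never states such an effect, so these figures are illustrations under an assumption and not findings about the plan.

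The survey figures are also imperfect. They compare two age groups in one survey year, not a followed cohort, and the Background describes them as disease needing treatment, which may not match ICDAS 4 to 6 with treated teeth included. That makes the 12-point increment, and all that rests on it, approximate. It does not rescue the 24%: the Sample size section itself uses the same 32% as the proportion with caries, and the conflict disappears only if true entry prevalence is 24% or lower. Nothing in the article suggests that for these schools.

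**Conclusion.** The point holds for the basis of the power claim. The control rate comes from the entry age, the endpoint is three years later on a cumulative index, and the stated intervention-arm rate lies below the expected baseline. The calculation reproduces; its inputs do not fit the outcome.

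The numerical effect is moderate. With 8 points kept at 44% v 36%, unadjusted power is 84.5 to 88.3% at 40 schools and 86.2 to 89.8% at 42. With baseline caries allowed for, power for 8 points exceeds 99%, and about 4.3 points is detectable at 42 schools. What changes most is the meaning of the target: about two thirds of new cases prevented, where 32% v 24% suggests one quarter.

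The unadjusted figures assume the age-15 survey rate, the plan's contamination rule, ICC and attrition. The adjusted figures further assume 32% prevalence at entry, 12 points of new caries, and the same ICC for new cases.

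**What to change.** Rewrite the sample-size paragraph:

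- Take the three-year control prevalence from the age-15 figures, weighted to the FSM mix of the recruited schools.
- State the expected baseline prevalence. Baseline data are collected before each school is randomised, so the observed figure, pooled over both year groups, can be used or checked against.
- Express the target as a reduction in new D4–6MFT cases, with the matching absolute difference at three years.
- Report the power, or the difference detectable with 90% power, that 42 schools give under the baseline-adjusted primary model, and say which cluster size the design effect uses.
- Remove the statement of 90% power for 32% v 24%.

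The cost is a recalculation and some rewording. No extra schools or pupils are needed, and neither the outcome nor the primary model changes. The required share of new cases prevented will look more demanding than one quarter, while the detectable absolute difference is likely to be smaller than 8 points.
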